#### Measures related to clinician responsiveness within primary care encounters

Clinician’s responsiveness within the clinical encounter will be assessed by rating “informativeness”, participatory decision-making, and partnership building. Overall informativeness will be rated on a 5-point Likert scale by two independent raters from recordings using [name] previously validated measure based on whether the clinician fully discusses what is causing the patient’s problem, the clinician explains everything to the patient, the clinician is very informative about the patient’s health, and the clinician’s recommendations are clear and easy to understand (score 4 to 20) [34, 35]. ACP-specific informativeness is adapted from this measure and uses the following three items: the clinician thoroughly explained everything about the ACP topic discussed, the clinician was very informative about ACP, and the clinician’s explanations about ACP are very clear (score 3 to 15). Clinician’s participatory decision-making/partnership building is adapted from Kaplan by [name] [34, 35]. For this measure, independent raters will decide on a 1 to 10 scale (1 = not at all and 10 = a great deal) whether the clinician involved the Veteran in the decisions, gave the Veteran a sense of control over medical care, and asked the Veteran to take some responsibility for ACP or medical care (scores 3 to 30).

#### Measures related to barriers and facilitators of ACP and PREPARE dissemination

Perceived barriers to engagement in ACP behaviors are assessed with a 10-item survey of the common barriers defined in our prior work and other studies [25].

#### Input about implementation

Input about implementation is assessed at 6 months by asking Veterans in the PREPARE arm questions about the acceptability and usability of PREPARE (for example, when and where to review ACP materials, and which PREPARE materials did you use and would recommend). For Veterans in the control arm, we ask about implementation of the ACP materials (for example, when and where to review ACP materials). For Veterans in the PREPARE arm, similar questions are asked of their surrogate decision-makers about the Veterans’ use of the PREPARE materials and the surrogates’ opinions.

## Outcomes and Sample Size Calculations

### Primary outcome

The primary outcome is advance directive documentation in the medical record. This outcome was selected based on prior studies that have shown that advance directive interventions can increase documentation. A meta-analysis demonstrated a pooled effect size of 0.50 (95 % CI; 0.17-0.83) suggesting a positive effect associated with advance directive interventions [36]. One RCT of an ACP workbook in older Veterans also demonstrated an increase in living wills documented from 23 % in controls to 48 % in the intervention group (*P* < .001); and ACP notes from 24 % to 47 % (*P* < .001) [37]. Consistent with results from prior studies, our pilot study showed that a literacy appropriate advance directive doubled completion rates from baseline [12]. From SFVAMC administrative data, 11 % of the potential study sample had an advance directive in their medical record. We assume that after being included in the study, the control group may have an advance directive documentation rate of 15 %. If we assume doubling of the percent of ACP discussion notes between groups (what we consider clinically significant), a sample size of 350, or 175 in each arm, will afford us 92 % power with a two-tailed alpha of 0.05 to detect an elevation in rate of advance directive documentation from 15 % in controls to 30 % in the PREPARE group and 80 % power to detect a difference of 15 % in controls versus 27 % in the PREPARE group. After accounting for an estimated 15 % attrition rate, including death at 6 months (based on prior work) [12], our recruitment target is 410 Veterans or 205 in each arm.

### Secondary outcomes

The secondary outcomes of this study include a comprehensive range of five specific ACP behaviors: 1) identification of a surrogate, 2) identification of values and goals, 3) choosing the level of leeway or flexibility in decision-making for the surrogate, 4) communicating this information with clinicians and surrogate decision-makers, and 5) documenting one’s wishes. We hypothesize that the scores from these ACP engagement items could be 50 % higher in the PREPARE group compared to the control group. Based on a pilot, the mean engagement scores for older outpatients were 30.7 points out of 57 ± SD of 10. Therefore, we expect a mean score as high as 40 points, a 10-point average difference between PREPARE and controls. However, even an increase of three points may represent a new action in any of the five domains. Using a two-tailed alpha of 0.05, 175 veterans in each randomization group will give us > 99.9 % power to detect a 10-point difference in engagement score, 96 % power to detect a four-point difference, and 80 % power to detect a three-point difference. A sample size of 350 will also allow us to assess each of the five domains of the preparation engagement survey separately as dichotomous variables, “action taken/no action taken”. If we assume a doubling of the percent of Veterans who “took action” within each of the five domains, using a two-tailed alpha of 0.05, we estimate that 175 veterans in each randomization group will give 92 % power to detect a doubling in the percent of Veterans who “took action” from 15 % (controls) to 30 % (PREPARE group) and 88 % power to detect a difference of 15 % versus 27 %. Taking into account an anticipated 15 % drop out as describe above, our anticipated 410 Veterans or 205 in each arm will provide us ample power to assess these outcomes.

The sample size of 350 Veterans will also allow adequate power to assess interactions based on potential moderating variables (race/ethnicity, literacy, gender) for our outcomes. We also anticipate very low intra-clinician correlations due to clustering or contamination; randomization is at the patient level not at the clinician level, and intra-clinician correlation values for patient attitudes and knowledge are typically quite low even in physician-level cluster randomized trials (for example, 0.015) [38]. Furthermore, as we have a potential pool of 115 clinicians, most clinicians will care for no more than one to three eligible Veterans and thus, there will be negligible loss of effective sample size accounting for clustering and contamination.

In exploratory analysis to corroborate Veteran reports of activation, we will attempt to recruit 144 surrogates (72 in each arm) anticipating that 20 % of Veterans will not have identified a surrogate based on pilot data, 15 % of Veterans will be lost to follow-up, and 30 % of surrogates will refuse. For patient activation within clinical encounters, we will attempt to audio-record 200 Veterans (100 in each group) to account for potential 25 % of enrolled Veteran and 25 % clinician refusal rates. For input about implementation, we anticipate recruiting 175 Veterans in the PREPARE arm (accounting for a 15 % drop-out at 6 months) and 72 of PREPARE arm Veteran’s surrogates.

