Although the easy-to-read advance directive was shown to be an improvement over standard forms, through additional formative work, we found that most patients go through a series of ACP behavioral steps that extend beyond simply filling out an advance directive. For example, 6 months after exposure to the easy-to-read advance directive, only 13 % completed an advance directive whereas 61 % of older adults contemplated ACP, 56 % discussed ACP with family or friends and 22 % discussed ACP with clinicians [14]. These data support the need to engage patients in a full range of ACP activities in addition to having them complete legal advance directive forms.

Based on our prior work [15] and the work of others [16, 17], we developed and published an updated paradigm of comprehensive ACP that shifts the focus from completion of advance directives to preparing patients to communicate their goals of care with surrogates and to actively participate with clinicians in making the best possible in-the-moment decisions [11]. To operationalize this new paradigm, we created an easy-to-read, culturally-appropriate website called PREPARE (www.prepareforyourcare.org). PREPARE is targeted to a 5^th^- grade reading level and was designed to be completed outside of a clinical setting without supervision or facilitation. PREPARE includes communication training on how to 1) choose and ask a surrogate; 2) clarify and communicate one’s values; 3) discuss leeway in surrogate’s decisions (allow surrogates to use their best judgment); 4) inform clinicians, family, and friends of one’s decisions; and 5) ask clinicians appropriate questions to make informed medical choices [11]. Extensive videos are used to demonstrate, through modeling, how to make ACP decisions and to communicate with surrogates and clinicians [15, 18–20]. Our pilot findings showed that, among diverse older adults, PREPARE significantly improved engagement and behavior change in ACP. Furthermore, it was rated a 9 out of 10 for ease of use, despite limited health literacy and lack of computer experience in this cohort of older adults [15].

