### Intervention and control conditions

After the baseline interview, participants in the PREPARE arm review the PREPARE website (www.prepareforyourcare.org) in the research offices. Research staff are available to answer questions, but participants are asked to go through the PREPARE website (Steps 1 through 5) on their own and in its entirety. As participants progress through the website, PREPARE asks questions about overall life values and goals for medical care. At the end of the program, the participant is asked to make an action plan to do one ACP task in the next weeks to months. At the end of the interview, research staff print out the action plan and a summary of the Veteran’s medical wishes and compile this into a folder that also contains the PREPARE pamphlet, booklet, DVD, and the log-in code to the website. The PREPARE DVD contains the same information found on the website, but without interactive or tailored functionality. PREPARE arm participants are also given an easy-to-read advance directive to review and take home (http://www.iha4health.org/our-services/advance-directive/) [13]. Participants in the control arm are only given the advance directive, are asked to review it for at least 10 minutes and to take it home. The control arm is not given any information about the PREPARE materials. One to 3 days before the Veteran’s next scheduled primary care appointment, research staff call the PREPARE arm participants to remind them to bring in their action plan, summary of wishes and advance directive to their doctor’s appointment. For the control arm, research staff members only remind Veterans about their upcoming primary care appointment.

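### Secondary-outcome power uses a 15 % control rate and a doubling for all five action domains, which conflicts with the article's own rates for the communication domain

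*Protocol article*

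**What the plan says.** The Secondary outcomes section lists five behaviours: identifying a surrogate, identifying values and goals, choosing leeway, communicating with clinicians and surrogates, and documenting wishes. It then plans a yes/no analysis of each: "A sample size of 350 will also allow us to assess each of the five domains of the preparation engagement survey separately as dichotomous variables". One effect is assumed for all five: "If we assume a doubling of the percent of Veterans who “took action” within each of the five domains". The test level and group size are common to all of them: "within each of the five domains, using a two-tailed alpha of 0.05, we estimate that 175 veterans in each randomization group". The power is given as 92 % for a doubling "from 15 % (controls) to 30 % (PREPARE group) and 88 % power to detect a difference of 15 % versus 27" %. The paragraph ends by calling the power for these outcomes ample.

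The section gives no source for 15 % as a rate of self-reported action. The same percentages appear in the Primary outcome section, where they concern chart documentation. There, "11 % of the potential study sample had an advance directive in their medical record", and the authors then assume that "the control group may have an advance directive documentation rate of 15" %.

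The Background reports what people did 6 months after exposure to the easy-to-read directive: 13 % completed one, 56 % "discussed ACP with family or friends and" 22 % did so with clinicians. That directive is the control condition here. Under Intervention and control conditions, "Participants in the control arm are only given the advance directive, are asked to review it for at least 10 minutes and to take it" […].

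**The concern.** The Background uses these rates to argue that planning steps differ widely in how often people take them. The power paragraph then gives every step a rate close to that of form completion. For communication, the article's own figures after the control material are 22 % and 56 %, not 15 %.

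Two things follow if the higher rate applies. A doubling cannot occur, because 2 × 56 % = 112 %. A given absolute difference is also harder to detect, because the binomial variance is larger near 50 % than near 15 %.

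The Aims section treats the secondary outcomes as equal in clinical importance to the primary one. A reader who relies on the general assurance of ample power could give a non-significant communication result more weight than it can bear.

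**Working it through.** **Inputs.** n = 175 per arm, two-sided α = 0.05, and the rates 15, 27 and 30 % (Primary outcome and Secondary outcomes). Control rates of 13, 22 and 56 % after the easy-to-read directive (Background).

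**Formula** (two proportions, normal approximation, pooled variance under the null, p̄ the mean of the two rates):

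power = Φ{ [ |p₂ − p₁| − 1.96·√(2p̄(1 − p̄)/n) ] / √([p₁(1 − p₁) + p₂(1 − p₂)]/n) }

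**Step 1: the plan's own figures.**
- 15 v 30 %: (0.150 − 0.0875)/0.0439 = 1.42, power 92.3 %. The stated 92 % reproduces.
- 15 v 27 %: (0.120 − 0.0853)/0.0431 = 0.80, power 79.0 % (unpooled 79.6 %, arcsine 79.5 %). The 80 % in the Primary outcome section agrees. The 88 % in the Secondary outcomes section, for the same rates, n and α, does not. A one-sided test gives 86.9 %, and 205 per arm gives 85.0 %, so neither explains it.

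**Step 2: communication domain at the Background rates.**

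| Control | PREPARE | Difference | Power |
|---|---|---|---|
| 56 % | 71 % | 15 points | 83.3 % |
| 56 % | 68 % | 12 points | 63.9 % |
| 22 % | 44 % (doubling) | 22 points | 99.4 % |
| 22 % | 37 % | 15 points | 87.1 % |
| 22 % | 34 % | 12 points | 70.7 % |

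For example, 56 v 71 % gives (0.150 − 0.1009)/0.0508 = 0.97, and Φ(0.97) ≈ 0.83. For 80 % power, a control rate of 56 % needs about 70.4 % in the PREPARE arm (14.4 points), and 22 % needs about 35.5 % (13.5 points).

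**Step 3: which rate applies.** Clinicians and surrogates are named in one domain. If either discussion counts as action, the control rate is at least that of the more common one, 56 %. If both are required, it is at most that of the rarer one, 22 %. The article does not give the scoring rule.

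**Step 4: the other domains.** For documentation, the Background's 13 % is close to 15 %, and a doubling (13 v 26 %) has 87.0 % power. No action rates are given for surrogate, values or leeway. Searching over all control rates with 175 per arm, power for a 15-point difference is lowest at 42.5 v 57.5 %: (0.150 − 0.1048)/0.0528 = 0.86, or 80.4 %. For 12 points it is lowest at 44 v 56 %: (0.120 − 0.1048)/0.0531 = 0.29, or 61.3 %.

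**The case against.** The strongest reply is that the evidence touches one domain out of five. This stands: 56 % and 22 % both describe communication, and documentation is near 15 %. A reader might also infer a conflict for surrogate identification, because the sample-size text for surrogates expects only 20 % of Veterans to have none identified. That figure does not separate surrogates chosen before enrolment from those chosen later, whereas follow-up asks about actions since randomization. It is therefore not a control rate for this outcome.

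Second, a different control rate does not always mean low power. This stands too. At 22 % the plan's own effect, a doubling, has more power than stated, and a 15-point difference keeps at least 80 % at any control rate. Much of the gap between the stated 88 % and the 12-point results is the arithmetic error: even at 15 % the power is about 79 %.

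Third, the rates come from earlier work with the directive, which the Background places at a county hospital, and friends or family are not the same as surrogate decision-makers. The transfer is an assumption. The plan does, however, rely on the same line of work for attrition and for the doubling of completion rates.

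Fourth, the power statement is conditional, its 92 % is correct for its inputs, and the planned analysis is a mixed effects logistic model rather than a two-proportion test. That is fair. But the closing claim of ample power carries no condition, and the simple calculation is the one the article itself presents.

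**Conclusion.** The point holds for the communication domain. The single assumption of 15 % doubling to 30 % does not fit the article's own rates after the control arm's directive. If a family or surrogate discussion alone counts as action, the assumed effect is impossible at a control rate of 56 % or more. At 56 %, power is 83 % for 15 points and 64 % for 12. If both discussions are required, the rate is at most 22 %, and a doubling from 22 % has 99 % power.

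A reader might go further and conclude that the stated power fails for all five domains, or that the trial is too small. The documents support neither. Three domains have no action rates, documentation is consistent with about 15 %, and the sample size rests on the primary outcome. That the 15 % was carried over from the documentation outcome is an inference from identical figures; the article does not say so.

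The result assumes that the earlier rates apply to these Veterans and that a two-proportion calculation with 175 per arm is an adequate guide. Separately, and with no such assumption, 88 % for 15 v 27 % is wrong on its own inputs.

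**What to change.** In the Secondary outcomes paragraph:

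- Keep 15 v 30 % (92 %) for the documentation domain only.
- For communication, drop doubling as the effect and give power for absolute differences at both control rates: 15 points, 87 % at 22 % and 83 % at 56 %; 12 points, 71 % and 64 %. State which discussions count as action.
- For the three domains without data, state that 15 points has at least 80 % power at any control rate and that 12 points may have as little as about 61 %. A 50 % control rate should not be shown as the worst case: 50 v 65 % gives 81.3 %, above the 80.4 % minimum.
- Limit the claim of ample power to differences of about 15 points or more.
- Correct 88 % for 15 v 27 % to about 79–80 %, in line with the Primary outcome section.

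The cost is a rewritten paragraph with less favourable figures. Recruitment of the 410 Veterans is complete, and neither the sample size nor the analysis changes.

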### Data analysis

#### RCT efficacy analysis

Our primary analyses will compare advance directive completion rates and change in engagement in the five ACP behaviors (see Primary outcome section) using behavior change measure scores on a 5-point Likert scale (analyzed as average Likert scores and total scores of 57 to 285) and action measure scores using yes and no responses (scores 0 to 25) from baseline to 1 week, and 3, and 6 months between study arms. We first will use means, medians, and ranges to describe continuous variables, and we will use proportions to describe categorical and dichotomous variables. Baseline comparability of the two groups will then be assessed using t-tests for continuous variables and chi-square tests for proportions. To examine the outcomes between the two study arms longitudinally, we will use mixed effects linear, Poisson, or negative binomial regression for continuous outcome measures and mixed effects logistic regression for dichotomous measures. The mixed effects models will include a random effect for subjects and fixed effects for the primary modeling terms of time, study arm, and an interaction term of study arm and time. We will treat the time variable in three different ways: (i) our first model will encode the time variable as a dummy variable for baseline versus the post-intervention time points; (ii) we will next model time in a continuous linear fashion; (iii) we will lastly consider an arbitrary time course by treating time as a categorical factor variable. We will also adjust for the randomization blocking factors of health literacy (limited versus adequate) and race (white versus non-white) [39] and for any predictor variables that differ between study arms at baseline. We will also include random physician intercepts to account for nesting of patients within physicians. We will consider including random effects for the primary modeling terms of time, study arm, and their interaction. Modeling decisions (for example, which mean structure to use and which random effects to include) will be based on comparing values of the Akaike Information Criterion. Models will be fit using the xt routines in Stata. Mediation analyses will use Stata’s mediation package, which allows estimation of the average causal mediation effect using a potential outcomes framework with either continuous or binary outcomes and allows for sensitivity analyses with respect to violation of the sequential ignorability assumption [40]. Moderating variables will be tested with interaction terms.

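### The 88% power stated for 15% versus 27% in the secondary outcomes should be about 79–80%, and the engagement-score effect sizes in the same paragraph need reconciling

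*Protocol article*

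**What the plan says.** All the power statements use the same design inputs. The Primary outcome section has "a sample size of 350, or 175 in each arm", two-tailed alpha 0.05. The Secondary outcomes section repeats them: "using a two-tailed alpha of 0.05, we estimate that 175 veterans in each randomization group".

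For 15% versus 27% the article gives two answers:
- Primary outcome: "80 % power to detect a difference of 15 % in controls versus 27 % in the PREPARE group".
- Secondary outcomes, for the proportion taking action in each domain: "and 88 % power to detect a difference of 15 % versus 27" per cent.

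For the engagement score, Secondary outcomes hypothesises that scores "could be 50 % higher in the PREPARE group compared to the control group". It cites a pilot mean of 30.7 out of 57 with an SD of 10, and continues: "Therefore, we expect a mean score as high as 40 points, a 10-point average difference between PREPARE and controls". It then gives more than 99.9% power for 10 points, 96% for 4 and 80% for 3.

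The RCT efficacy analysis section describes the scores to be analysed. The behaviour change measures are "analyzed as average Likert scores and total scores of 57 to 285", and the action measures are scored 0 to 25.

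**The concern.** The same comparison cannot have both 80% and 88% power. The article calls the secondary outcomes as clinically meaningful as the primary one, places change in engagement within its primary analyses, and ends the paragraph by claiming ample power. A reader weighing a null result in one action domain would therefore take the chance of missing a rise from 15% to 27% to be 12%, when it is about 21%.

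The engagement-score text raises two further questions. The step from a 50% increase to a mean of 40 is presented as a deduction, but the numbers do not follow. The point differences are given on a scale that the analysis section does not name, so a reader cannot tell what a 3- or 4-point difference means for the scores that will be reported.

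**Working it through.** **Inputs.** 175 per arm and two-sided alpha 0.05 (both outcome sections); control rate 15%, PREPARE rate 30% or 27% (both sections); pilot mean 30.7 and SD 10 (Secondary outcomes).

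**1. Two proportions.** With p̄ the mean of the two rates and z = 1.96:

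power = Φ{ [ (p2 − p1) − z·√(2p̄(1−p̄)/n) ] / √( [p1(1−p1) + p2(1−p2)]/n ) }

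*The companion figure first, 15% vs 30%.* p̄ = 0.225; null SE = √(0.34875/175) = 0.0446; alternative SE = √(0.3375/175) = 0.0439. Power = Φ[(0.150 − 0.0875)/0.0439] = Φ(1.42) = 92.3%. The stated 92% reproduces.

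*The disputed figure, 15% vs 27%.* p̄ = 0.21; null SE = √(0.3318/175) = 0.0435; alternative SE = √(0.3246/175) = 0.0431. Power = Φ[(0.120 − 0.0853)/0.0431] = Φ(0.80) = 79.0%. The 80% under Primary outcome agrees within rounding; the 88% does not.

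Other ways of reaching 88% for 15% vs 27%:

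| Variant | Power |
|---|---|
| Unpooled variance, n = 175 | 79.6% |
| Arcsine, n = 175 | 79.4% |
| Exact enumeration of the chi-square test, n = 175 | 79.4% |
| Log odds ratio, n = 175 | 77.8% |
| Continuity-corrected, n = 175 | 74.9% |
| Pooled, n = 205 (no attrition) | 84.9% |
| One-sided 0.05, n = 175 | 86.9% |

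The one-sided test comes closest, but the sentence says two-tailed, and its companion 92% would then be 95.9%. A two-sided 88% needs about 225 per arm (88.1%), or at 175 per arm a PREPARE rate between 28.5% (86.8%) and 29% (88.9%).

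**2. Engagement-score power.** SE of the difference = 10·√(2/175) = 1.069; power = Φ(Δ/1.069 − 1.96).
- Δ = 3 (0.3 SD): Φ(0.85) = 80.1%; stated 80%.
- Δ = 4 (0.4 SD): Φ(1.78) = 96.3%; stated 96%.
- Δ = 10 (1.0 SD): above 99.9%; stated as such.

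All three reproduce.

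**3. The 50% and the 40 points.** 30.7 × 1.5 = 46.05, a difference of 15.35. The stated 40 is 40/30.7 = 1.30, so 30% higher (9.3 points). A full 10-point difference gives 40.7, which is 33% higher. Power exceeds 99.9% at 9.3, 10 or 15.35 points.

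**4. The scale.** A mean of 30.7 lies below the minimum of the 57–285 total, above the maximum of the 0–25 action score, and outside any average on a 5-point item. The SD of 10 and the point differences therefore belong to none of the scores listed for analysis.

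**The case against.** The strongest reply is that little turns on this. The 88% concerns a fallback scenario for a secondary outcome, the right figure is printed in the section just before it, and the main claim for the five domains, a doubling from 15% to 30% at 92% power, is correct. All of that stands. It limits the weight of the point but does not rescue the figure.

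On the engagement score, the wording is loose (scores could be higher, a mean as high as 40), and the article never says outright that 30.7 is the expected control mean. That is fair, but the paragraph itself uses 30.7 to derive the 40 and the 10 points, and on that use 50% does not follow. It is also fair that 57 equals the minimum of the 57–285 total, which suggests the same items under another pilot scoring. The article does not say so, and a fuller protocol may.

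A reader might infer more than the text supports:
- *That the whole paragraph is wrong.* Four of its five power figures reproduce.
- *That the trial is undersized.* The article states that the sample size was calculated on the primary outcome; 350 and then 410 come from there.
- *That the engagement power figures are meaningless.* They hold at 175 per arm for any roughly continuous score, as power for 0.3, 0.4 and 1.0 SD. Only the translation into points is lost.

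**Conclusion.** The 88% is an isolated arithmetical error. Under the stated inputs the power is about 79% (74.9% to 79.6% across the two-sided methods tried), roughly 9 percentage points below the stated value, and it contradicts the 80% under Primary outcome. This assumes independent arms with 1:1 allocation and a simple two-sample comparison, which is the basis on which the neighbouring figures reproduce.

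The mismatch between 50% and 40 points is a real inconsistency if the pilot mean is read as the control mean, but it changes no power or sample-size figure. The 57-point score is a real mismatch with the RCT efficacy analysis section, and its effect is confined to interpreting the point differences.

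This is a minor correction to the text. It does not touch the primary-outcome calculation or the target of 410.

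**What to change.** 1. In Secondary outcomes, replace 88% with 80% so that it matches Primary outcome, or print 79% in both sections. Changing only one of them to 79% would leave a new mismatch.
2. Reconcile the engagement hypothesis. Either change 50% to about 30% and keep 40 points with a difference of roughly 10, or keep 50% and change both numbers, to about 46 points and a difference of about 15.
3. State the engagement-score power in SD units: with 175 per arm, 80% for 0.30 SD, 96% for 0.40 SD and more than 99.9% for 1.0 SD. Say how the pilot score out of 57 relates to the 57–285, average Likert and 0–25 scores. Point equivalents on those scales need SDs that the article does not give; the sponsor can add them if it holds them.

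The cost is a few words of text. One stated power becomes less favourable. Recruitment of the 410 Veterans is already complete, and no design or analysis decision changes.

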The SFVAMC Veteran population consists of  approximately 4 % women [1]. Therefore, we increased recruitment of women by working closely with the SFVAMC Women’s Clinic and oversampling women through our patient recruitment call lists. To ensure a diverse sample, we also oversampled minorities in an attempt to obtain a cohort of 50 % white and 50 % non-white Veterans. Oversampling is feasible as the racial/ethnic variation of SFVAMC outpatients is approximately 55 % white, 29 % black, 8 % Latino, 6 % Asian/Pacific Islander, and 2 % other [26].

For a subset of enrolled participants, we also include Veteran’s self-identified surrogate decision-makers. Surrogates are included if the Veteran identifies her or him and gives the study team permission to contact them. Surrogates are excluded if they had dementia or are blind, deaf, or psychotic as determined by the study staff (Table 1).

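### The stated adequate power for moderator interactions does not hold for the primary outcome, the dichotomous action domains or 3- to 4-point engagement-score interactions

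*Protocol article*

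**What the plan says.** Under Secondary outcomes, after the power figures for the engagement score and the five action domains, the article states that the sample of 350 "will also allow adequate power to assess interactions based on potential moderating variables (race/ethnicity, literacy, gender) for our outcomes". The analysis is planned: under RCT efficacy analysis, "Moderating variables will be tested with interaction terms".

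The figures that size the trial are all for main effects. Under Primary outcome, the article says that 350 Veterans, split evenly between the arms, "will afford us 92 % power with a two-tailed alpha of 0.05". That figure is for documentation rates of 15% (control) and 30% (PREPARE); for 15% and 27% it gives 80%. Under Secondary outcomes, each action domain is sized on the same 15% versus 30%. For the score, "the mean engagement scores for older outpatients were 30.7 points out of 57 ± SD of 10", with a hoped-for difference of 10 points and power also given for 4 and 3 points.

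On subgroup shares, the Participants section aims for half white and half non-white. It describes the source population as "approximately 4 % women" and says women are oversampled, without a target. No share with limited health literacy is given.

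**The concern.** Between two equal halves of a sample, an interaction has about twice the standard error of the overall treatment effect, and more if one subgroup is small. A trial with 92% power for a 15-point main effect therefore cannot have comparable power for a 15-point interaction. The sentence nevertheless claims adequacy for the outcomes in general and for three moderators, including gender.

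The design gives weight to these moderators: randomization is stratified by literacy and race/ethnicity, and women and minorities are oversampled. Readers will look for consistency of effect across these groups. A printed statement of adequate power invites them to take a non-significant interaction as evidence of equal benefit, when such a result would be likely even if PREPARE had no effect in one group.

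**Working it through.** **Inputs.** From the article: 350 analysed, 175 per arm, two-sided alpha 0.05, 15% versus 30%, score SD 10, score differences of 10, 4 and 3 points, a 50:50 race target, and about 4% women in the source population. Assumed: 4%, 10% or 20% women in the trial, and equal allocation within subgroups.

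**1. The article's main-effect figures.** For proportions, power = Φ{[Δ − 1.96√(2p̄(1−p̄)/n)] / √([p₁(1−p₁) + p₂(1−p₂)]/n)}.
- 15% v 30%, n = 175: (0.15 − 1.96 × 0.0446)/0.0439 = 1.42, giving 92.3% (stated 92%).
- 15% v 27%: 79.0% (stated 80% under Primary outcome).
- Score: SE = 10√(2/175) = 1.069. Four points gives 96.3% (stated 96%), three points 80.1% (stated 80%), and ten points above 99.9%.

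The same simple two-group methods are used below.

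**2. Binary outcomes, even split (87.5 per arm-by-moderator cell).** Two ways of placing a 15-point interaction:
- A: 15→30 in one subgroup, 15→15 in the other.
- B: 15→37.5 and 15→22.5, so that the average effect is still 15 points.

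Risk difference, SE = √(Σ p(1−p)/87.5):
- A: √(0.5925/87.5) = 0.0823; 0.15/0.0823 = 1.82; power 44.6%.
- B: √(0.66375/87.5) = 0.0871; 0.15/0.0871 = 1.72; power 40.6%.

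Log odds, SE = √(Σ 1/[87.5 p(1−p)]):
- A: difference in log odds ratios 0.887; SE 0.569; ratio 1.56; power 34.5%.
- B: difference 0.726; SE 0.542; ratio 1.34; power 26.8%.

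If the interaction is instead set to the full main-effect log odds ratio of 0.887 (half that effect in one subgroup, one and a half times in the other), power is 37%. No even-split case exceeds 45%.

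Interaction detectable with 80% power, using the 15% and 30% variances in both subgroups: 2.80 × √(2 × 0.3375/87.5) = 2.80 × 0.0878 = 24.6 points.

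**3. Binary outcomes, gender.** The cells become 175f and 175(1−f) for a share f of women. The ranges cover A and B, with the larger effect in either sex.

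| Women (assumed) | Risk difference | Log odds |
|---|---|---|
| 4% | 10–12% | 8–10% |
| 10% | 17–21% | 12–17% |
| 20% | 27–33% | 18–25% |

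At 4% there would be 14 women, 7 per arm, and about one expected event among control women (7 × 0.15 = 1.05). The normal approximation is crude there, so that row is indicative only.

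**4. Engagement score.** SE = 10√(4/(350f) + 4/(350(1−f))).

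| Subgroup share | SE | 3 points | 4 points | 10 points | Detectable at 80% |
|---|---|---|---|---|---|
| 50% | 2.14 | 29% | 46% | 99.7% | 6.0 |
| 20% | 2.67 | 20% | 32% | 96% | 7.5 |
| 10% | 3.56 | 13% | 20% | 80% | 10.0 |
| 4% | 5.46 | 9% | 11% | 45% | 15.3 |

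**5. No attrition.** With all 410 analysed at an even split, a 15-point interaction has 46–51% power on the risk-difference scale and 31–39% on the log-odds scale.

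**The case against.** A reader might infer that power for any interaction as large as the main effect is at most about 45%, whatever the outcome. The documents do not support that. The sentence covers the engagement score too, and there an interaction equal to the hoped-for 10-point difference has 99.7% power at an even split and 80% at a 10% subgroup. An interaction of a full standard deviation is optimistic, but for that case the claim is right. The criticism must therefore name the outcome.

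A reader might also take the 4% figure as the share of women in the trial and quote a single low power for gender. The 4% describes the source population. Women were oversampled and prioritised on call lists, so the achieved share is unknown and the gender figures are an assumed range. The same caution applies to literacy.

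Three further points have some weight. The article plans mixed models with repeated survey measurements, which could raise power somewhat for survey outcomes; it quantifies no such gain. It is a condensed article, and calculations may exist elsewhere. But the objection is not that a calculation is missing: the article's own inputs contradict the stated property for the primary outcome. Finally, the article lists no moderator hypothesis and does not say that a non-significant interaction will be read as equal effect. That misreading is a risk, not something planned, and neither the primary nor the secondary hypotheses depend on this sentence.

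**Conclusion.** The sentence is wrong as written. Adequate power for moderator interactions does not hold for advance directive documentation, for the five dichotomous action domains sized on the same rates, or for score interactions of 3–4 points. At the most favourable split, a 15-point interaction on a binary outcome has about 41–45% power (risk difference) or 27–35% (log odds). Only interactions of about 25 points reach 80%. For gender the figures are lower: roughly 8–12%, 12–21% or 18–33% if women make up 4%, 10% or 20% of the sample.

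The claim stands for a score interaction near 10 points, except in a very small subgroup (45% at a 4% share).

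These results rest on single-time-point Wald tests, 350 analysed, equal allocation within subgroups, and assumed shares for women. Analysing all 410 would not change the conclusion for the binary outcomes.

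**What to change.** Replace the sentence with text of this kind:

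> Moderator analyses are exploratory. For the binary outcomes, power for an interaction equal to the 15-point main effect is at most about 45% at an even split, and lower for smaller subgroups such as women. For the engagement score, the interaction detectable with 80% power is about 6 points at an even split and about 10 points for a 10% subgroup. Interaction estimates will be reported with 95% confidence intervals, and a non-significant interaction will not be taken as evidence of equal effect.

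The cost is text only. Recruitment of the 410 Veterans is complete, and nothing in the design, data collection or primary analysis changes. The price is a less favourable stated property of the trial.
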